## Abstract

**Background:**

Public safety personnel have regular and often intense exposure to potentially traumatic events at work, especially workplace violence in the case of correctional workers. Subsequently, correctional workers are at higher risk of developing mental health problems such as posttraumatic stress disorder. Public safety personnel are up to 4 times more likely to experience suicidal ideation, suicidal attempts, and death by suicide compared to the general population. Despite this high prevalence, help-seeking behaviors from public safety personnel are low due to stigma and irregular work hours limiting access to care. Innovative treatments are needed to address these challenges.

**Objective:**

This study will investigate the efficacy of an electronically delivered cognitive behavioral therapy (e-CBT) program tailored to correctional workers’ mental health problems.

**Methods:**

This study is composed of 4 phases. In phase 1, we will interview correctional workers individually and in focus groups to identify personal, social, and cultural factors affecting their mental health and barriers to care. Phase 2 will use the information gathered from the interviews to develop gender- and diagnosis-specific e-CBT modules. These will be presented to a new group of participants who will provide further feedback on their usability and accessibility. In phase 3, we will randomly assign participants to either an e-CBT or treatment as usual arm. The program will be evaluated with validated symptomatology questionnaires and interviews. Phase 4 will use this additional information to fine-tune the e-CBT modules for a larger-scale randomized controlled trial design comparing the e-CBT program to in-person CBT. All e-CBT modules will be delivered through a secure online platform.

**Results:**

The study received ethics approval in December 2020, and participant recruitment began in March 2021. Participant recruitment has been conducted through targeted advertisements and physician referrals. To date, there have been 15 participants recruited for Phase 1, and it is expected to conclude in July 2021, with phase 2 beginning in September 2021. Complete data collection and analysis from all phases are expected to conclude by July 2023. Linear and binomial regression (for continuous and categorical outcomes, respectively) will be conducted along with interpretive qualitative methods.

**Conclusions:**

If proven efficacious and feasible, this e-CBT program can provide a high-quality and clinically validated resource to address the mental health problems of correctional workers. Additionally, findings can contribute to the development of innovative treatments for other public safety professions.

**Trial Registration:**

ClinicalTrials.gov NCT04666974; https://www.clinicaltrials.gov/ct2/show/NCT04666974

**International Registered Report Identifier (IRRID):**

DERR1-10.2196/30845

## Introduction

### Background

Public safety personnel (PSP) have regular and often intense exposure to traumatic events and are at higher risk for developing mental health disorders including posttraumatic stress disorder (PTSD), major depressive disorder (MDD), generalized anxiety disorder (GAD), and drug and alcohol use disorders [1]. PSPs are up to 4 times more likely to experience suicidal ideation, suicidal attempts, and death by suicide compared to the general population [2]. Correctional workers (CWs) are at a particularly elevated risk of developing mental health disorders, as they work in a hostile environment with an increased prevalence of violence [3]. A survey found that over 98% of CWs have had at least one encounter with job-related traumatic events, frequently involving exposure to serious injury or death; casualties; unusual sights, sounds, and circumstances; first-hand knowledge of the victim(s); and threats to their safety and security [4]. It was also found that CWs, on average, will experience approximately 28 traumatic events during their career [4]. Many CWs feel there are not enough organizational policies to debrief following the occurrence of such difficult situations, along with a lack of after-hour counselling, leaving them concerned with the limited support available through their employee assistance programs [5]. The absence of sufficient organizational policies exacerbates the effects of violent incidents on CWs, leading to PTSD being 3 times more prevalent in CWs compared to the general population [6-8]. Therefore, the need to address this mental health crisis in CWs must be a top priority.

Psychotherapy, and more specifically, cognitive behavioral therapy (CBT), is the first-line treatment for various anxiety disorders, including PTSD [9-17]. Psychotherapy can be more cost-effective, decrease relapse prevalence, outperform many pharmacotherapies, and be the intervention of preference for many patients when treating anxiety disorders [18-23]. CBT is one of the most widely investigated and practiced forms of psychotherapy and is effective in reducing the deleterious symptoms of mood and anxiety disorders [24].

While CBT has a well-established efficacy in improving various mental health disorder symptoms, many patients do not receive treatment [25]. This is due to the multitude of barriers to receiving treatment, which include psychological, social, geographical, financial, and systemic factors [26]. Despite the high rate of mental health disorders in PSPs, their willingness to seek treatment is low because of the stigma attached to mental health in their profession [27,28]. Many PSPs feel discredited by seeking treatment for their mental health and feel an expectation from their job to tolerate their symptoms [28,29]. Among those who do seek help, they face unique barriers including irregular work hours, limiting their access to resources otherwise available to the public. In many cases, the publicly available options, such as group CBT, add to the stigma of receiving care, especially in smaller cities.

A promising solution to address these barriers is the asynchronous, text-based, module-driven, diagnosis-specific, electronic delivery of CBT (e-CBT). In recent years, there has been an increased interest in researching the efficacy of e-CBT, due to its ability to address many barriers associated with in-person CBT [30-32]. Delivering e-CBT asynchronously allows for therapy to be accessed at a convenient time for the patient from the comfort of their own home. e-CBT content can be adapted to a multitude of languages and cultures, meeting the needs of more patients. Moreover, the private nature of e-CBT can reduce the stigma of receiving care [28,33]. e-CBT has been shown to effectively treat a variety of mental health disorders, supported by several meta-analyses [34-37]. Regarding depression and anxiety disorders, e-CBT can be efficacious as a singular or adjunctive treatment [38-40]. Additionally, e-CBT has also been shown to effectively address PTSD symptoms [41-45]. These findings are promising as e-CBT techniques are cost-effective, are geographically and temporally accessible, have shorter waiting times for treatment, reduce stigma, increase help-seeking among patients, and can increase treatment adherence [46,47]. More importantly, the treatment outcomes of e-CBT are suggested to be comparable to in-person psychotherapy for individuals with GAD [38]. Regarding scalability, e-CBT can offer up to 70%-80% time savings for therapists [47].

There are many forms of e-CBT, including unguided self-help, guided self-help (standardized program with support from a mental health professional), and individualized therapy (tailors therapy modules to patient needs based on an entry interview) [48-50]. The length and mode of delivery vary between programs; however, they all utilize the same strategies as in-person CBT. While all programs have some form of efficacy, their impact can vary greatly. It has been found that the major factor affecting program efficacy is the level of care provider engagement [51]. While many studies suggest even self-guided content can be beneficial, more therapist engagement is related to higher treatment efficacy [51,52]. Therapy outcomes (ie, symptom reduction, remission) are up to 3 times higher in supervised e-CBT compared to self-guided methods [53]. Therefore, a supervised e-CBT approach is needed to effectively address the mental health needs of this PSP population.

### Objectives

Each phase has a respective objective. In phase 1, the aim is to understand CWs’ mental health challenges and barriers to receiving care. In phase 2, we will create e-CBT modules to address the CW-specific mental health problems found in phase 1. In phase 3, the aim is to evaluate the e-CBT program efficacy compared to treatment as usual (TAU). In phase 4, we will evaluate the e-CBT program efficacy compared to in-person CBT.

## Methods

### Design

This study is split into 4 phases with the first 2 using a qualitative approach to uncover mental health challenges and barriers to care faced by CWs, along with the usability of the e-CBT modules developed. These phases will use qualitative interviews and focus groups to collect data. Phase 3 will use a randomized controlled trial (RCT) design, with participants being allocated to either an e-CBT or TAU arm. In phase 4, an RCT design will be employed again, comparing the efficacy of the e-CBT arm to an in-person CBT arm. This study has been registered with ClinicalTrials.gov (NCT04666974).

### Recruitment

In phase 1, a group of experienced CWs (n=5) will be initially recruited. These CWs will have in-depth knowledge of CW problems and will be chosen in consultation with CW union members. Moreover, members of this research team have extensive experience working with Correction Services Canada and will use their expertise to select suitable participants. Following this, a larger group of CWs (n=40; 20 men, 20 women) will be recruited for individual and focus group interviews. Recruitment will be conducted using flyers (distributed in the workplace), advertisements in specialized journals, union representatives, and word of mouth.

In phase 2, CWs (n=20; 10 men, 10 women) will be recruited using the same methods as in phase 1.

In phase 3, CWs (n=100; 50 men, 50 women) will be recruited using the same materials as in the previous phases; however, participants will also be accepted based on physician referrals.

In phase 4, CWs (n=100; 50 men, 50 women) will be recruited using the same methods as in phase 3. However, an additional step will be taken to ensure eligibility by conducting a comprehensive interview by a psychiatrist, further validated by a structured interview performed by a trained research assistant.

### Inclusion/Exclusion Criteria

Participants will undergo a comprehensive initial mental health assessment by a psychiatrist on the research team. These assessments will occur either in person or through video calls. Diagnoses will be identified using the structured Mini-International Neuropsychiatric Interview (MINI) performed by a trained research assistant and a psychiatric assessment conducted by a psychiatrist on the research team. Inclusion criteria include 18-55 years of age at the start of the study; diagnosis of MDD, GAD, or PTSD according to the Diagnostic and Statistical Manual of Mental Disorders, 5th Edition (DSM-5); competence to consent and participate; ability to speak and read English; and consistent and reliable access to the internet [54]. Exclusion criteria include diagnosis of hypomanic/manic episodes, psychosis, severe alcohol or substance use disorder, and active suicidal/homicidal ideation.

### Phase 1

An expert end-user group of CWs (n=5) will help the research team across all phases of this project. These experts will have in-depth knowledge of CW problems and will be chosen in consultation with CW union members. A new set of CWs (n=40; 20 men, 20 women) will be recruited to participate in individual interviews and then in virtual focus groups through Microsoft Teams as this platform is approved for security reasons by the Queen’s University Health Science and Affiliated Teaching Hospitals Research Ethics Board (HSREB). These interviews will be used to identify the main mental health challenges and the best methods to address them in the context of different groups of CWs (eg, administrative staff, operational workers, direct vs indirect contact with prisoners, working in a prison vs working in probation offices) and investigate the barriers specific to each group. Each individual will be independently interviewed by a trained research assistant hired for the project (60-90–minute duration). Interviews will occur remotely via a secure video conference with Microsoft Teams. Questions will include topics of the level of interaction with prisoners, types and frequency of violence at work, sexual assault, work condition (staffing, shift length, relationship with superiors and co-workers, workload, over-crowdedness), socioeconomic factors (race, gender, language, sexuality, religious discrimination), mental challenges, resources (training, peer support, and professional help) and frequency they use them, reasons for refraining to use resources, preferred method of support (onsite vs offsite, individual vs group), and attitude towards online care (willing to do so and what content they want to be covered). Information gathered through individual interviews will form the basis for further focus group discussions via Microsoft Teams.

Following individual interviews, 5 half-day focus groups (8 participants per group, 2 exclusively female, 2 exclusively male, 1 sex balanced) will be conducted to gather more information regarding issues uncovered in individual interviews. These focus groups will occur remotely via video conference with Microsoft Teams. A list of challenges to be addressed in phases 2-4 will be formed from these interviews. The principal investigator, 1 psychiatrist, 1 psychologist, 1 research assistant, and at least 2 members of the end-user expert group will attend each group meeting to form a better understanding of the problems faced by each group. All interviews and focus group discussions will be recorded and transcribed verbatim for further discussion at the investigative team meetings.

### Phase 2

Following the first round of content development, e-CBT modules will be presented to the end-user expert group and a smaller number of interview/focus group participants (n=20; 10 men, 10 women) for feedback. Each participant will be asked to provide feedback on 1 of the 6 therapeutic modules regarding content, form, presentation, examples, and helpfulness, based on the challenges it tries to address. All feedback will be summarized and compiled by research assistants and discussed in 6 separate focus group discussions attended by the principal investigator, 1 psychiatrist, 1 psychologist, 1 research assistant, and at least 2 members of the end-user expert group. Each participant is requested to attend 2 virtual focus group discussions on the module they have not seen yet or commented on. This is done to ensure each participant can provide feedback on all gender-specific therapy contents. A list of recommended changes to each module will be developed through these discussions. Recommendations will be reviewed by the principal investigator, co-applicants, and the knowledge users for clinical validation. The final changes, compiled by clinicians, will be applied to the e-CBT module.

### Phase 3

CWs (n=100; 50 men, 50 women) meeting the inclusion/exclusion criteria will complete a set of socioeconomic, demographic, and the following clinical questionnaires (primary diagnosis dependent) at baseline: Depression and Anxiety Stress Scale - 42 Item (DASS-42), Quality of Life Satisfaction and Enjoyment Questionnaire (Q-LES-Q), Quick Inventory of Depressive Symptoms Self Report - 16 Item (QIDS-SR16), Patient Health Questionnaire - 9 Item (PHQ-9), Generalized Anxiety Disorder - 7 Item (GAD-7), and PTSD Checklist for the DSM-5 (PCL-5) [55-60]. Questionnaires and e-CBT modules will be completed through the Online Psychotherapy Tool (OPTT; OPTT Inc.), a secure, cloud-based, mental health care delivery, online platform. OPTT can be accessed from various devices (ie, computer, cellphone, tablet) and internet browsers. Following the initial assessment, participants will be randomly allocated to the e-CBT + TAU (n=50; 25 men, 25 women) or TAU (n=50; 25 men, 25 women) arm.

Participants in the e-CBT group will be assigned to 1 of the 6 therapy modules based on their gender and diagnosis (ie, female/male; GAD/MDD/PTSD). All e-CBT sessions will be completed through OPTT. Sessions will be designed to mirror in-person CBT content and consist of approximately 30 slides and interactive therapist videos (40-60–minute completion time), with 12 sessions in total (1 module per week). The modules will focus on standard aspects of CBT (the connection between thoughts, behaviors, emotions, physical reactions, and environment) and incorporate different skills into each session (eg, mindfulness, goal setting, activity scheduling). Each participant will be assigned a specific therapist who will be their care liaison through the program. Each week, the clinician will send the new e-CBT session to the participant through OPTT on a predetermined day of the week. Each of these sessions will include a homework assignment that the participant must send back to their clinician by a predetermined date to gain access to the next session. Upon receiving the homework submission, the clinician will review the participant’s work and provide individualized feedback on their performance. This feedback will be sent back to the participant with their new e-CBT module the following week. Clinician feedback will follow a structured format and take approximately 15 minutes per patient, allowing for increased scalability.

Participants in both arms will complete the symptomology questionnaires every 2 weeks along with 6-month and 12-month follow-ups. Additionally, participants in the e-CBT arm will complete a qualitative questionnaire regarding their experience using OPTT. These questions will relate to the aesthetic appeal of OPTT, the intuitiveness of OPTT, technical support experience, OPTT navigation and simplicity, and the kinds of devices used to access therapy. Information from this qualitative questionnaire will be used to fine-tune the e-CBT modules for phase 4.

### Phase 4

At baseline, participants (n=100; 50 men, 50 women) will complete the same socioeconomic, demographic, and clinical questionnaires as in phase 3 through OPTT. Following the initial assessment, participants will be randomly allocated to either the e-CBT + TAU (n=50; 25 men, 25 women) or in-person CBT + TAU (n=50; 25 men, 25 women) arm. Participants in the TAU arm will continue with current lifestyle choices (ie, physical activity, diet, socialization) and current treatments (ie, pharmacotherapy, meditation) for the duration of the program.

Participants in the e-CBT arm will receive a specific program based on their primary diagnosis and gender (male/female; GAD/MDD/PTSD). Participants will be assigned a specific therapist who will be their care liaison throughout the program. Participants in the in-person CBT arm will receive similar content, homework, and feedback compared to the e-CBT arm. All in-person CBT sessions (60-75–minute completion times) will be delivered by a trained professional.

Participants in both arms will complete the symptomology questionnaires biweekly (same as in phase 3) along with 6-month and 12-month follow-ups. Following week 12 (posttreatment), participants will also complete an additional MINI. Additionally, participants in the e-CBT arm will complete the same qualitative questionnaire relating to their experience using OPTT. These responses will be discussed with the end-user expert group to form recommendations for improving the e-CBT modules through OPTT.

### Training

Therapists will be trained in psychotherapy delivery and supervised by a psychiatrist on the research team who has extensive experience in e-CBT. To ensure consistency of care, therapists will learn a standardized pathway of care and undergo sample training sessions before interacting with patients. Feedback templates will vary between e-CBT modules with therapists providing personalization directly related to their participants’ work. Before submission, all feedback will be reviewed and approved by a psychiatrist on the research team.

### Outcomes

Phases 1 and 2 will be completed using qualitative individual interviews along with focus groups. Phases 3 and 4 will be completed using the quantitative methodology and will be based on the findings from phases 1 and 2.

Phase 1 aims to evaluate mental health challenges and barriers to receiving care faced by CWs. This information will be used to create the e-CBT modules that will be presented to participants in phase 2, where the usability of these modules will be investigated.

In phases 3 and 4, the primary outcome will be comparing changes in symptom severity from baseline to posttreatment between e-CBT and TAU/in-person CBT arms, respectively. This will be evaluated using the DASS-42, Q-LES-Q, QIDS-SR16, PHQ-9, GAD-7, and PCL-5. These questionnaires will be completed biweekly starting at baseline until posttreatment (week 12), followed by 6-month and 12-month follow-ups.

The secondary outcomes of phases 3 and 4 will be evaluating how personal, social, and demographic factors can impact treatment experience. This will be investigated using the data from the qualitative questionnaires.

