### Analysis

Qualitative analysis of interview and focus group data (phases 1 and 2) will be performed using an iterative analysis process where investigators will review interview transcripts and search for key phrases, ideas, and themes directly pertaining to the research questions. Similarly, the qualitative comments and feedback obtained from questionnaires in phases 3 and 4 will also be transcribed and analyzed for themes. The information collected in phases 1 and 2 will be used to develop the e-CBT modules, with the information collected through phases 3 and 4 being used to finalize the format of the e-CBT (if necessary).

In phases 3 and 4, the relationship between socioeconomic status, demographic factors, and mental health challenges faced by CWs will be investigated. Questionnaire data will initially be examined for missing, nonsensical, and outlying variables and corrected where possible. Missing data will be treated as missing and not imputed (ie, will be analyzed on a per-protocol basis).

Following this, the symptomatology questionnaires (DASS-42, Q-LES-Q, QIDS-SR16, PHQ-9, GAD-7, and PCL-5) will be analyzed based on score change from baseline to posttreatment, 6-month follow-up, and 12-month follow-up. Questionnaire scores will be calculated for each time point, and then the changes between the times will be assessed using multivariate repeated measures analysis of variance (MANOVA). Comparisons will then be made between the e-CBT and control arms using linear regression models while controlling for demographic variables (eg, age, gender).

Factoring in anticipated dropouts, recruitment numbers have been purposely oversampled. From previous research in similar patient populations, dropouts can be expected to be up to 25% [61]. Given that there are 6 specialized versions of the e-CBT modules with different symptom questionnaires, it is difficult to calculate a single sample size or provide specific power calculations. However, using the PCL-5 as an example as it will be common to all participants, a 10-point change is considered clinically significant [62]. Therefore, a sample size of 30 participants in each arm will be sufficient for detecting significant results with *P*=.05 and a power of 0.8.

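### Six unranked questionnaires form the posttreatment primary outcome of each RCT with no stated success rule; if any one significant result counted, the false-positive chance would be about 11–26% rather than 5%

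*Protocol article*

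**What the plan says.** In Outcomes, the article states for phases 3 and 4 that "the primary outcome will be comparing changes in symptom severity from baseline to posttreatment between e-CBT and TAU/in-person CBT arms, respectively". The next sentence gives the instruments: "This will be evaluated using the DASS-42, Q-LES-Q, QIDS-SR16, PHQ-9, GAD-7, and PCL-5". No order or lead is given. The only secondary outcomes named concern treatment experience and come from the qualitative questionnaires, so no quantitative scale sits below the primary tier.

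In Analysis, the same six scales "will be analyzed based on score change from baseline to posttreatment, 6-month follow-up, and 12-month follow-up". Changes over time go into a repeated measures MANOVA. After that, "Comparisons will then be made between the e-CBT and control arms using linear regression models while controlling for demographic variables". Neither sentence names a deciding scale, makes one analysis a gate for another, or says what result would be read as efficacy. The PCL-5 appears in the sample-size paragraph only as an example, chosen because everyone completes it.

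In Phase 3, the instruments are introduced as "the following clinical questionnaires (primary diagnosis dependent) at baseline", so it is also unclear which participants contribute to which scale.

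**The concern.** The choice of primary endpoint decides what the trial can claim. Here the text makes that choice, and it chooses six measures of equal standing. A reader of the results could not tell whether success means a difference on one scale, on most, on all, or on the scale matching the participant's diagnosis. If one favourable scale out of six may carry the efficacy claim, the 5% level no longer describes the risk of a false claim, and the scale to emphasise can be picked after the results are known.

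Two features of the list add to this. The Q-LES-Q is by its own title about quality of life, so it does not measure the stated outcome, symptom severity. The DASS-42 and the QIDS-SR16 both cover depression by title, with nothing to say which leads. The article itself remarks that the module versions and their differing questionnaires make a single sample size hard to calculate; having no single primary endpoint has the same effect.

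**Working it through.** **Inputs from the article.** Six primary scales at one primary time point, posttreatment at week 12 (Outcomes). Significance level .05, power 0.8, a 10-point PCL-5 change, 30 per arm, and dropout up to 25% (Analysis). Allocation 50 per arm (Phase 3 and Phase 4).

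**Assumptions.** Two-sided tests, since the side is not stated; one test per scale; success if any one is significant; equal correlation between the six test statistics, varied from 0 to 0.9. The article gives no correlations.

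**1. The plan's own figure.** For two means, n per arm = 2(z₀.₉₇₅ + z₀.₈₀)² SD²/Δ². The article gives no SD, so I solved for it: SD = 10/[(1.960 + 0.842) × √(2/30)] = 13.8. The stated 30 per arm is therefore right if the SD is about 13.8. For SDs of 10, 15 and 20, n would be 16, 36 and 63. The figure can be neither confirmed nor refuted, but it is a calculation for one scale tested at .05.

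**2. Chance of at least one false positive among six scales at week 12.** With independent tests this is 1 − 0.95⁶ = 1 − 0.735 = 0.265. For correlated tests it was simulated with 1,000,000 draws of equicorrelated normal statistics:

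| Assumed correlation | Any of six significant (two-sided .05) |
|---|---|
| 0 | 26.5% |
| 0.3 | 24.1% |
| 0.5 | 20.6% |
| 0.7 | 16.3% |
| 0.8 | 13.9% |
| 0.9 | 10.9% |

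This is 2.2 to 5.3 times the nominal 5%. Counting only differences in favour of e-CBT, the rate runs from 14.1% (independent) to 5.4% (correlation 0.9) against a nominal 2.5%, which is a similar ratio.

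**3. If each diagnosis group used only three scales.** The rate is 1 − 0.95³ = 14.3% if independent and 9.8% at correlation 0.8.

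**4. Cost of keeping all six with Bonferroni.** The level per scale is 0.05/6 = 0.0083. At the implied SD of 13.8, n = 2(2.638 + 0.842)² × 13.8²/10² = 46.1, so 47 per arm instead of 30. After 25% dropout 50 × 0.75 = 37.5 per arm remain, and power is about 69%. At 30 per arm it is 57%.

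**The case against.** The strongest reply is that this is a condensed article and the analysis plan is not shown. Multiplicity methods commonly sit there, so the absence of an adjustment is no fault in itself. That stands. It does not cover the endpoint: the article itself fixes six co-equal measures as the primary outcome, and an analysis plan that later picked one would be changing what is stated here.

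It can also be said that the inflation needs a success rule the article never states. That is correct: requiring all six scales to be significant would not inflate the error at all. The figures are therefore conditional. The lack of any rule is what is certain.

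Some stronger readings are tempting but not supported:

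- A reader might count three time points and arrive at 18 primary tests, with 1 − 0.95¹⁸ = 60%. Outcomes limits the primary contrast to baseline to posttreatment. The 6- and 12-month changes are analysed, but they are not named as primary.
- A reader might take it as stated that each scale has its own regression tested at .05. The article says only that linear regression models will be used, and .05 appears only in the sample-size sentence.
- A reader might infer that every scale is analysed over everyone, mixing participants who have the target condition with those who do not. The wording in Phase 3 ("clinical questionnaires (primary diagnosis dependent) at baseline") leaves this open.
- A reader might apply the same figures to phase 4. That phase sets e-CBT against in-person CBT, and the Discussion hopes to find them comparable. A falsely significant difference is not the main error behind such a claim.

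**Conclusion.** The point holds for the primary outcome at week 12. Six unranked scales, one of which is not a symptom scale, serve as the primary outcome of each RCT, and no success rule is stated. On an any-one-of-six reading the two-sided false-positive chance is about 11–26% instead of 5%. It is toward the lower end if the scales are strongly correlated, which is plausible where they overlap on depression. The size rests on the assumed correlations, on one test per scale, and on the any-one rule. It bears mainly on the claim in phase 3 that e-CBT is superior to treatment as usual. In phase 4 the undefined endpoint remains, but the figures carry over less directly.

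**What to change.** Name one primary endpoint at week 12 for each RCT before outcome data are seen. Two options use data already planned:

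- **Diagnosis-matched scale.** PCL-5 for PTSD, PHQ-9 for MDD and GAD-7 for GAD, each standardised by its baseline SD and analysed in one model with diagnosis as a factor. This uses all participants and fits the diagnosis-specific modules. The DASS-42, QIDS-SR16 and Q-LES-Q lose primary status. The stated 30 per arm rests on a raw 10-point PCL-5 change, so the sample size must be re-expressed in SD units. Raw-scale results should be reported alongside.
- **One scale completed by all**, such as the PCL-5 already used for the sample size. This keeps the present basis, though the SD still has to be stated, and five scales lose primary status. For participants with MDD or GAD it does not target the condition their module treats.

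Make the remaining scales, the Q-LES-Q (as quality of life) and the 6- and 12-month contrasts secondary, with Holm adjustment or labelled exploratory. State which participants complete which scale.

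Either option restores a 5% level for the primary claim without more participants on multiplicity grounds, whereas Bonferroni over six scales needs 47 per arm. The cost is an amendment to the protocol, analysis plan and registry wording, plus the restated sample size where it applies. The article reports only phase 1 recruitment, so at that date the choice could still be made ahead of any randomised data.
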